### Study design, setting and participants

This randomised control trial protocol has been developed in accordance with the SPIRIT (Standard protocol items: recommendations for interventional trials) guidelines for protocol reporting [31]. The SPIRIT checklist is available as supporting information (see Supplementary Material 1).

The study will be performed at the Laboratory of Behavioral Medicine of Neuroscience Institute (NI) of the Lithuanian University of Health Sciences (LUHS) in Palanga, Lithuania. The individuals with CAD attending a rehabilitation program at the Palanga Clinic of the LUHS NI will be invited to participate in this study. Individuals who comply with the following inclusion criteria will be considered for inclusion in the study: (1) age 18 years and older, (2) diagnosis of CAD, (3) participation in the cardiac rehabilitation program, (4) ability to hear, speak and read in Lithuanian, and (5) signed informed consent. The selection of age ensures that the research specifically targets adults, since some reactions to treatments may differ across different age cohorts, particularly very young individuals. By including individuals who are actively engaged in a cardiac rehabilitation programme, the research will focus on a particular subgroup of the population with CAD who will receive an intervention aiming to improve standard rehabilitation practices. Requiring participants to hear, speak, and read in Lithuanian will ensure language consistency throughout the study and that the investigation is culturally appropriate and contextually relevant. A signed informed consent form will serve as documentation that participation in this particular study is voluntary.

Exclusion criteria will comprise (1) coronary artery bypass graft surgery, other cardiac surgery, (2) cognitive disabilities or other severe comorbidities, (3) unstable cardiovascular status. Focusing on individuals with CAD without the potentially confounding effects of recent surgical interventions will ensure a relatively stable subjects’ group. Cardiac surgeries can introduce variability in health status, recovery, and medication regimens, which may impact the study outcomes [30]. Individuals with cognitive dysfunction or severe comorbidities, especially in CAD [29], may introduce confounding factors that affect their ability to comprehend and adhere to the study protocol. Importantly, excluding individuals with unstable cardiovascular status will prioritise safety of those individuals who undergo rehabilitation and will align with ethical considerations.

### Study procedure

The patients will be informed about the purpose and procedures of the study before signing the informed consent form. The breakdown structure of the study activities is presented in Fig. 1. A cardiologist will consult each patient about their eligibility to take part in the experiment, and their functional capacity will also be assessed. Following the consultation with the cardiologist, additional baseline assessments will be performed to evaluate demographic and clinical characteristics, weather sensitivity, Type D personality, subjective mental health status, and basal cortisol level. Basal cortisol level will be registered by testing cortisol concentration in saliva in the morning and in afternoon, one day prior to the experiment. After baseline measurements, patients will be randomly assigned to two groups: walking outdoors (OUT) or walking indoors (IN). OUT group will walk in the city park located within a 2–3 min walk of the LUHS NI Palanga Clinic along a pre-designated route. IN group will walk in a gym on a treadmill. The order and sequence of measurements within each trial will be the same (Fig. 2).

**Fig. 1 Fig1:**
[figure not shown]
Study design: A breakdown structure depicting chronological steps (activities) to attain each of the predefined objectives

### Randomisation

Depending on the date and time of consent to take part in the study, every second individual will be consecutively assigned to one of the conditions (e.g., the first individual will walk outdoors, the second will walk indoors, the third will walk outdoors, a fourth will walk indoors again and so on) without any prior preference or prioritization whatsoever.

### Experiment procedure

On the day of the experiment (Fig. 2), we will evaluate the effect of walking in different environments on hemodynamic parameters, stress level (according to cortisol concentration in saliva), and mood. In the morning, the patient will be fitted with a long-term blood pressure device, which will be removed the next morning. In this way, the patient will also receive detailed information about their hemodynamics. Both a collection of saliva samples and a mood assessment will be performed immediately before and after the intervention (walking). A cold pressure test (short immersion of patient’s hand into a cold container) will then be administered, followed by a third mood assessment. The third saliva sample will be collected 20 min after the cold pressure test. Cortisol levels rise progressively after a few minutes (about 10 min) of stimulation and peak between 10 and 30 min after stress termination [32, 33].

Participants in the OUT group will be instructed to keep a comfortable walking speed and to enjoy the walk and the surroundings. Participants in the IN group will be introduced to the treadmill and encouraged to choose a walking speed like that of leisurely outdoor walking. All participants will be informed that they will be accompanied by the researcher (at a distance) during the intervention to monitor their walking time, minimize the impact of social interaction, and control any potential well-being or health problems.

**Fig. 2 Fig2:**
[figure not shown]
The experiment sequence of the study Note. BP monitor – continuous blood pressure measurement; C – saliva collection for cortisol analysis; M – mood; PI – pain intensity; Intervention – walking outdoor or indoor

### Measurements

A set of validated instruments are listed in Table 1 and will be used in this investigation. These tools have all been vvalidated and are often used in Lithuanian clinical and research settings. The research will involve a variety of actions and measures, as listed in Table 1.

**Table 1 Tab1:** Steps and measures of the study

Step	Variable	Instrument	Measure	Procedure duration
1.	Weather sensitivity	Questionnaire (short form)	The Palanga Weather Sensitivity Self-Assessment Diary (PSAD-WS) will be completed to assess weather sensitivity [22]. PSAD-WS is an 11-item (general) three-factor tool for collecting information regarding weather sensitivity in patients with CAD. The three subscales reflected (1) psychological symptoms, (2) cardiac symptoms and (3) physical. Also, patients will be asked a single question: “Do you feel the weather changes?” with possible answers of “NO” or “YES”.	up to 2 min
2.	Cortisol level	Saliva samples will be obtained using “SaliCap Set“ releasing the saliva into the sampling tubes. Samples will then be stored at -70^o^C and cortisol levels will be determined in a licensed laboratory using commercial reagent kits.	To assess hypothalamic pituitary adrenocortial (HPA) axis activity, cortisol will be sampled and assayed from participants’ saliva.	up to 20 min
3.	Sociodemographic characteristics and clinical history	Medical records	Age, sex, education, medical history [i.e., New York Heart Association (NYHA) functional class, history of ACS, and angina pectoris class], and medication.	up to 15 min
4.	Functional capacity	The six-minute walk test (6MWT) [34]	The 6MWT will be performed in a 30 m hallway and will be monitored by a physiotherapist. The patient will instructed to remain calm, to have taken his/her medications and to wear comfortable clothing and shoes. All tests will be performed between 8:00 am and 12:00 am in a quiet indoor hallway with a flat straight floor. The floor will be marked in 1 m increments and total distance covered will be recorded. Participants will be asked to walk at their own pace, while attempting to cover as much ground as possible within the allotted six minutes. Every minute, a physiotherapist will encourage subjects to continue walking and inform them of the time elapsed, using standardized phrases (“You are doing well” or “Keep up the good work”). The patient’s heart rate, BP will be measured before and after the test. Any symptoms experienced by the patient during this test will also be recorded (Borg scale) [35]. The distance walked will be recorded after the test.	up to 10 min
5.	Mental health outcomes	Patient Health Questionnaire (PHQ) [36, 37]	The PHQ assesses 8 diagnoses, divided into threshold disorders (disorders that correspond to specific diagnoses in the Diagnostic and Statistical Manual of Mental Disorders, Fourth Edition, specifically major depressive disorder, panic disorder, other anxiety disorder, and bulimia nervosa) and subthreshold disorders (disorders for which criteria encompass fewer symptoms than are required for any specific diagnoses in Diagnostic and Statistical Manual of Mental Disorders, Fourth Edition, specifically other depressive disorder, probable alcohol abuse or dependence, and somatoform and binge eating disorders). This questionnaire will be mainly treated to control our findings for confounding mental health status.	up to 15 min
6.	Type D personality	Type D Personality Scale (DS14) [38]	The DS14 is a 14-item self-rating questionnaire that consists of two 7-item subscales that are designed to measure personality traits of negative affectivity (NA) and social inhibition (SI), Each item is rated on a five-point Likert-type scale from 0 (false) to 4 (true) with scores ranging from 0 to 28 on each subscale. Scores equal or greater than 10 on both DS14 subscales of NA and SI, indicate Type D personality.	Up to 5 min
7.	Compulsive Personality	Compulsive Personality Assessment Scale (CPAS) [39]	The CPAS includes 8 items and measures the severity of obsessive-compulsive personality traits and tendencies. Each of the eight diagnostic criteria is scored on a Likert scale of 0 to 4, and the maximum total score of the CPAS is 32. Diagnosis of obsessive-compulsive personality disorder can be defined as a score of three (severe) or four (very severe) on at least four of the CPAS items.	Up to 3 min
8.	Cognitive function	Cambridge Neuropsychological Test Automated Battery [40]	CANTAB will be used to evaluate alterations in executive function as follows: - Motor screening Task (MOT) – sensorimotor function. - Cambridge Gambling Test – decision making (impulsivity, risk taking) - Delayed Matching to Sample – short-term visual recognition memory; - Intra-Extra Dimensional Set Shift (IED) – set-shifting, mental flexibility; - Match to Sample Visual Search (MTS) – attention and visual searching; - One Touch Stockings (OTS) – spatial planning and the working memory; - Rapid Visual Information Processing (RVP) – sustained attention; - Spatial Working Memory (SWM) – working memory. Tests have been validated in behavioral and psychopharmacological studies on healthy volunteers and in a range of patient groups [41].	up to 60 min
9.	Hemodynamic parameters	A long-term blood pressure (BP) device – The SOMNOtouch NIBP monitor	The SOMNOtouch NIBP monitor will be used to make a simultaneous, continuous, and non-reactive recording of BP, ECGs, and oxygen saturation thus a comparative analysis of several vital parameters will be provided. A long-term BP monitor will be placed on the patient at the beginning of the study.	Up to 24 h
10.	Mood	Visual Analog Scales (VAS) [42]	Participants simply will rate the intensity of the sensation on a scale from 0–100. VAS were chosen based on its applicability in experimental clinical studies.	Up to 1 min
11.	Cold pressure stress	Cold pressure test (CPT) [43]	CPT will be used to induce acute stress. Temperature and other environmental stressors are known to affect BP and heart rate. In this activity, participants will be performed the cold pressure test to demonstrate the changes in BP that follow an environmental stress. For cold stress, the subject will immerse his or her right hand in the ice-water bath (4 °C) to a point just above the elbow for 2 min. BP measurements will be obtained using a long-term BP device – the SOMNOtouch NIBP monitor on the wrist of the left hand at 0, 1, 2, and 4 min after the right hand will be removed from the ice-water bath.	Up to 8 min
12.	Pain intensity	Visual Analog Scales (VAS) [42]	After the CPT, study participants will be debriefed about the purpose of the study and the subjective measure of perceived efforts and perceived difficulty of the CPT will be collected by using VAS. The scales ranged from 0 (maximum difficulty/efforts) to 100 (minimum difficulty/efforts). VAS were chosen based on its applicability in experimental clinical studies and common use in combination with CPT [44].	Up to 1 min

### Sample size

Based on previous research in this area [45], considering the cortisol response to psychophysiological stress as a primary approach to detect a likely medium difference between groups effect (Cohen d = 0.5) and achieve sufficient power1 (1-ß err prob = 0.95) requires a sample of at least *n* = 82 subjects. Considering possible side variable of weather sensitivity and differences in natural conditions, likelihood of 4% attrition, the sample is planned to be doubled to *N* = 164 subjects. The enrollment duration - one year.

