However, natural environments may not always be restorative, despite the fact that people tend to recover more quickly from stress and mental fatigue in natural than in urban settings [16]. In fact, physical environment can heighten or ameliorate stress, while meteorological factors also cause a certain stress on the human body [17]. Changes in meteorological parameters may affect human hemodynamics and other factors adversely, thereby catalysing the event of an acute coronary syndrome [18]. To this extent, little is known about the restorative or exacerbating potential of natural environments for weather-sensitive (WS) individuals. Concerning reactions to weather variations, people can be divided into two main groups: weather-resistant and WS [19, 20]. The term “weather sensitivity” is used to define the impairment of well-being and/or incidence of symptoms or exacerbations of diseases in response to weather changes [21]. According to the results of our earlier study, almost 50% of individuals with CAD described themselves as being WS [22].

WS profile and the effects of walking in nature on the psychophysiological stress response in individuals with CAD (WE_SENSE_THE_NATURE) is a pioneer study, aiming to investigate how weather sensitivity and walking in different environments affects psychophysiological responses to the stress of individuals with CAD during rehabilitation. The proposed randomised control trial will provide insight on the influence of environmental exposure, as it is seldom investigated in association to heart disease.

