## Methods / design

### Aim

The aim of this study is to investigate how WS and walking in different environments affect psychophysiological responses to the stress of individuals with CAD during rehabilitation.

To achieve the main goal, we will aim to deliver a set of specific objectives:

Determining how walking outdoors (in a natural setting) affects the psychophysiological reactions to stress in individuals with CAD.Determining how walking indoors (in the gym) affects the psychophysiological reactions to stress in individuals with CAD.Investigating the associations between the psychophysiological reactions to stress of individuals with CAD and the walking environment, by accounting for their weather-sensitivity.Understanding the connections between mental flexibility and weather sensitivity in the context of personality characteristics and mental distress.

We hypothesize that: (1) the psychophysiological reactions to stress in people with CAD will differ between the experimental (walking outdoors) and the control group (walking indoors); (2) for the experimental group, we hypothesize that psychophysiological reactions to stress will differ between WS individuals and non-WS individuals, showing more favorable results in the latter subgroup (non-WS individuals); (3) for the control group, we hypothesize that psychophysiological reactions to stress will differ between WS individuals and non-WS individuals, showing more favorable results in the former subgroup (WS individuals). The fourth goal is exploratory and therefore has no hypothesis.

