clinical practice - using different types of environments in cardiac rehabilitation. If the hypotheses are confirmed, for weather-sensitive patients with CAD, it might be better to engage in physical activity in an indoor environment than in an outdoor one;sciences and education. Whilst the study will be carried out in Lithuania, it is hoped that the methods used and the results obtained will contribute to a better understanding of the problem analyses and will be useful for future insights and research not only in Lithuania, but also on an international level. It might also provide a foundation for new research studies looking into and beyond traditional risk factors identifying high-risk subgroups of patients with CAD vulnerable to stress.health services’ management - to the government and policymakers in planning and implementing actions to improve medical care services in rehabilitation and post-rehabilitation settings.

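### The trial is sized on one pooled OUT–IN effect although H2 and H3 imply that this effect differs by weather sensitivity, and no stated hypothesis tests the indoor-versus-outdoor contrast in WS patients that the Discussion would draw on

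*Protocol article*

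**What the plan says.** **Hypotheses (Aim).** H1 is an overall, non-directional comparison: reactions to stress "will differ between the experimental (walking outdoors) and the control group (walking indoors"). H2 concerns the outdoor arm only, "showing more favorable results in the latter subgroup (non-WS individuals"). H3 concerns the indoor arm only, "showing more favorable results in the former subgroup (WS individuals").

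**Sizing (Sample size).** The cortisol response is used "as a primary approach to detect a likely medium difference between groups effect (Cohen d = 0.5"). The power target is 0.95, and the section concludes that this "requires a sample of at least *n* = 82 subjects". The number is then doubled to 164. The reasons given are weather sensitivity as a possible side variable, differences in natural conditions, and 4% attrition. No effect size by WS status and no interaction effect is stated.

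**Prevalence (Background).** In the group's earlier study "almost 50% of individuals with CAD described themselves as being WS".

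**Analysis (Statistical analysis).** Two-sample tests are named for comparing groups, General Linear Modelling for several outcomes together, and regression for adjustment. No environment-by-WS term is named.

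**Intended use (Discussion).** The section offers this reading, conditional on H1 to H3 being borne out: "for weather-sensitive patients with CAD, it might be better to engage in physical activity in an indoor environment than in an outdoor one".

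**The concern.** Two of the three hypotheses say that weather sensitivity matters, and in opposite directions in the two arms. That is a statement about interaction. The sizing rests on one average effect, as if WS status did not change the effect of the walking environment. Two things follow.

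- **Power of the overall test.** If the effects in WS and non-WS patients pull apart, their average may be much smaller than 0.5. The H1 comparison would then have far less power than the section suggests. A non-significant overall result could be read as no effect of environment.
- **The practical conclusion.** The Discussion's statement is about OUT against IN among WS patients. H2 and H3 compare WS with non-WS patients inside one arm. These comparisons do not use the allocation to OUT or IN, and they do not answer the indoor-or-outdoor question for WS patients.

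**Working it through.** **Inputs.** From the protocol: d = 0.5, power 0.95, n = 82, N = 164 (Sample size); alternating 1:1 allocation, so 82 per arm (Randomisation); WS almost 50% (Background). Assumed, because not stated: alpha 0.05; two-sided, since H1 is non-directional; equal WS share in both arms; a common standard deviation (SD); and all subgroup effects. Positive effects favour OUT.

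**1. The plan's own figure.** A two-group t-test at d = 0.5 and power 0.95 needs about 105 per arm (210 in total) two-sided, so 82 is not reproduced under these settings. That is a separate matter. For this point, 82 v 82 at d = 0.5 gives power 0.89.

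**2. What H2 and H3 imply.** Write the four cell means with higher as more favourable.

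- H2: a = OUT(non-WS) - OUT(WS) > 0
- H3: b = IN(WS) - IN(non-WS) > 0
- Sum: a + b = [OUT - IN in non-WS] - [OUT - IN in WS] > 0

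So the environment effect differs by WS status by a + b. The sum does not fix the sign of the effect in either stratum.

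**3. H2 and H3 can both hold with WS patients better outdoors.** Take cell means in SD units (an illustration): OUT non-WS 1.00, OUT WS 0.75, IN WS 0.50, IN non-WS 0.25.

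- H2: 1.00 - 0.75 = 0.25 > 0. H3: 0.50 - 0.25 = 0.25 > 0.
- OUT - IN in WS: 0.75 - 0.50 = +0.25, favouring outdoors.
- OUT - IN in non-WS: 1.00 - 0.25 = +0.75. The average is 0.50, so H1 holds as well.

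All three hypotheses are true here, and the Discussion's statement about WS patients would be wrong.

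**4. Dilution of the pooled test.** Pooled d = (1 - p) × d(non-WS) + p × d(WS), with p the WS share. Power is from the noncentral t at 82 v 82, noncentrality = d × √(82/2). With p = 0.50 and d(non-WS) = +0.5:

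| d(WS) | Pooled d | Power, overall test |
|---|---|---|
| +0.5 | 0.500 | 0.89 |
| 0 | 0.250 | 0.36 |
| -0.25 | 0.125 | 0.13 |
| -0.5 | 0 | 0.05 (alpha) |

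For d(WS) = 0, -0.25 and -0.5, power is 0.42, 0.18 and 0.06 at p = 0.45, and 0.48, 0.25 and 0.10 at p = 0.40.

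**5. Pairs that lose nothing.** At p = 0.50, +0.75 / +0.25 averages 0.5, and 0 / -1.0 averages -0.5. Both leave power at 0.89. To keep a pooled 0.5 favouring OUT with d(WS) = 0, -0.25 or -0.5, the non-WS effect must be 1.0, 1.25 or 1.5.

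**6. What N = 164 offers by stratum.** With 41 per cell:

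- within one stratum (41 v 41), d = 0.5: power 0.61;
- interaction contrast, standard error √(4/41) = 0.312 SD: power 0.36, 0.67 and 0.89 for a difference of 0.5, 0.75 and 1.0 SD.

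**The case against.** **A reader might infer that, if the hypotheses are right, the overall test is likely to be null.** The documents do not support this. H1 is one of the hypotheses and says that the arms differ overall; a pooled effect of zero makes H1 false. Power reaches alpha only with equal and opposite effects in two equal halves, and the Background says almost 50%.

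**A reader might also infer that the hypotheses predict a reversal in WS patients.** H2 and H3 give an interaction, not a change of sign. The reversal rests on one Discussion sentence, worded as a possibility.

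**Nor does the sizing stand only when WS has no influence.** Any pair averaging 0.5 in absolute value keeps the same power, and H1 states no direction. The assumed 0.5 may already be meant as an average.

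**The plan does not ignore WS.** N was doubled partly on its account, one objective studies the walking environment with WS taken into account, and a General Linear Model could carry the interaction. Exact model terms are commonly left to an analysis plan. This stands, and it lowers the weight of the point. But doubling N does not restore a diluted average: with d = 0.25, the doubled sample has power 0.36. If the doubling was meant to give each WS stratum its own 82, the stratum power for d = 0.5 is 0.61, not 0.95. And the hypotheses as written still leave out the contrast that the Discussion would use.

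**Conclusion.** The point holds in limited form. The implied environment-by-WS interaction follows from H2 and H3 by algebra and needs no assumption. So does the gap between what those hypotheses compare (WS with non-WS within an arm) and what the Discussion would conclude (indoor against outdoor within WS patients).

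The loss of power is conditional. It rests on assumed subgroup effects, two-sided alpha 0.05, 82 v 82 and about half the patients WS. On those terms the overall test goes from 0.89 to 0.36 if WS patients have no environment effect, and to 0.13 if theirs is modestly negative, with the non-WS effect held at +0.5. It is no loss at all if the two effects average 0.5 in absolute value. The protocol's figures cannot say which case applies, and that is why the sizing text should say what its 0.5 averages over.

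**What to change.** 1. Keep N = 164 and the overall OUT–IN comparison for H1.
2. In the General Linear Model for the cortisol response, include arm, WS and arm-by-WS, and test the interaction. Name one baseline definition of WS in advance, because Table 1 collects two: the PSAD-WS questionnaire and a single yes/no question.
3. Report the OUT–IN difference with its confidence interval separately in WS and non-WS patients.
4. Base the Discussion's conclusion for WS patients on the OUT–IN contrast in the WS stratum, not on H2 and H3.
5. In Sample size, state that d = 0.5 is an average over WS and non-WS patients, that power for the overall test falls if the two effects pull apart, and that power within a stratum of 41 v 41 at d = 0.5 is about 0.61.

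**Cost.** No further patients or measurements, since WS is recorded at baseline. There is one more pre-specified test, and the stratum estimates are less precise: the standard error is √(2/41) = 0.22 SD, against √(2/82) = 0.16 SD overall.

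A joint 2-df test of arm and arm-by-WS is optional. If the effect is the same in both strata, it costs about 7 points of power (0.82 against 0.89). For the non-WS / WS pairs +0.5 / 0 and +0.5 / -0.25 it has 0.51 and 0.61, against 0.36 and 0.13 for the overall test. It would also change the meaning of H1 from an overall difference to a difference in at least one stratum, so it should not silently replace the H1 test.

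### Neither reading of the base figure of 82 gives the weather-sensitivity hypotheses 0.95 power: at N = 164, H2 and H3 each compare about 41 with 41 patients, with about 0.61 power at d = 0.5

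*Protocol article*

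**What the plan says.** The Sample size section gives one effect size, a "likely medium difference between groups effect (Cohen d = 0.5" in Cohen's notation, for the cortisol response. It gives one power, "1-ß err prob = 0.95", and concludes that this "requires a sample of at least *n* = 82 subjects". It then gives three reasons for enlarging the trial, with weather sensitivity first: "Considering possible side variable of weather sensitivity and differences in natural conditions, likelihood of 4% attrition, the sample is planned to be doubled". The result is that "the sample is planned to be doubled to *N* = 164 subjects".

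The Aim section states three hypotheses. H1 compares the outdoor (OUT) with the indoor (IN) arm. The other two are within-arm comparisons. H2 reads "for the experimental group, we hypothesize that psychophysiological reactions to stress will differ between WS individuals and non-WS individuals", with the better result predicted for non-WS patients. H3 reads "for the control group, we hypothesize that psychophysiological reactions to stress will differ between WS individuals and non-WS individuals", with the better result predicted for WS patients. Only the fourth goal is called exploratory.

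The Randomisation section alternates assignment one to one. The Background reports from the group's earlier study that "almost 50% of individuals with CAD described themselves as being WS". The visible text states no alpha, no sidedness and no separate power for H2 or H3.

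**The concern.** Weather sensitivity is the trial's distinctive question. It makes up two of the three hypotheses, and the Discussion builds a possible recommendation about where WS patients should exercise on those hypotheses being confirmed. A reader who sees one power figure of 0.95 and a sample doubled partly for weather sensitivity will take the trial to be well sized for it.

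H2 and H3 each use only half of the patients and split that half again. If their power is near 0.6, each misses a true medium effect about four times in ten. A significant result in one arm beside a null result in the other would then be a common outcome even when both effects are real, and it could be misread as an effect confined to one environment.

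**Working it through.** **Inputs**
- d = 0.5, power 0.95, base n = 82, N = 164, attrition 4%: Sample size.
- Allocation 1:1, so 82 per arm: Randomisation.
- WS share about 50%: Background. This gives about 41 WS and 41 non-WS per arm.
- After attrition: 164 × 0.96 = 157.4, so about 79 per arm, or 40 v 39.
- Assumed: alpha 0.05, unadjusted two-sample t test. Two-sided is the main case. One-sided is also shown because H2 and H3 name a direction.

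**Formula.** The noncentrality is δ = d × √(n₁n₂ / (n₁ + n₂)). Power is the probability that a noncentral t variable with n₁ + n₂ − 2 degrees of freedom exceeds the critical value.

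**Step 1: can the stated 82 be reproduced?** For d = 0.5 and power 0.95, the exact t calculation needs 105 per group (210 in total) two-sided, or 88 per group (176) one-sided. A paired t test needs 54 or 45. None of these is 82. The two readings of 82 give:

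| Reading of 82 | Groups | δ | Power two-sided | Power one-sided |
|---|---|---|---|---|
| Total | 41 v 41 | 0.5 × √20.5 = 2.26 | 0.609 | 0.726 |
| Per group | 82 v 82 | 0.5 × √41 = 3.20 | 0.889 | 0.939 |

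Values close to 82 arise only from settings that the text does not state. One is a group-by-time interaction over three time points with zero correlation, which gives 84.

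**Step 2: power of H2 and of H3 at N = 164**

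| WS v non-WS in one arm | Two-sided | One-sided |
|---|---|---|
| 41 v 41 (50% WS) | 0.609 | 0.726 |
| 40 v 39 (50% WS, after 4% attrition) | 0.593 | 0.711 |
| 33 v 49 (40% WS) | 0.592 | 0.711 |
| 25 v 57 (30% WS) | 0.540 | 0.663 |

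The two arms are independent, so the chance that both tests are significant is 0.609² = 0.37 two-sided, or 0.726² = 0.53 one-sided. With 41 v 41, power 0.95 needs d = 0.81 two-sided (0.73 one-sided). Power 0.80 two-sided needs d = 0.63.

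**Step 3: what does the doubling do?**
- If 82 is a total, each arm of 82 is the same size as the base calculation. Doubling would carry the base claim to each within-arm test, but that claim fails at source: 82 patients in all give 0.61.
- If 82 is per group, 164 is simply two arms of 82. Nothing has been added for weather sensitivity, natural conditions or attrition.

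**Step 4: could baseline adjustment close the gap?** With a baseline–outcome correlation r, the effective effect is d / √(1 − r²). For 41 v 41, two-sided, power is 0.73 at r = 0.5, 0.88 at r = 0.7, and reaches 0.95 at about r = 0.78.

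**Step 5: arm-by-WS interaction on all patients.** The standard error of the difference of differences is SD × √(4/41) = 0.312 SD. If both effects are 0.5 in opposite directions, the contrast is 1.0 SD and power is 0.889 (0.873 with 39 per cell, 0.834 with 30% WS). If only one arm has an effect of 0.5, power is 0.356.

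**The case against.** The strongest reply is that the protocol does not attach 0.95 to H2 or H3. The figure belongs to a between-group difference in cortisol response, and weather sensitivity appears in the sample-size text only as a side consideration alongside two others. This stands. A reader might infer that the trial promises 95% power for each WS hypothesis, and the document does not say so. What remains is narrower: 0.95 is the only power given, weather sensitivity is a stated reason for the enlargement, and H2 and H3 are stated as hypotheses and not as exploratory aims.

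A second inference is that the doubling itself is the error. This is not supported either. On the literal reading of 82 as a total, doubling is the right step for two within-arm tests and the fault lies in the base figure. On the per-group reading there is no real doubling.

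Third, the test model is unknown. Alpha and sidedness are not visible, a footnote attached to the word power is not shown, cortisol is measured before the walk, and General Linear Modelling is planned. Adjustment could raise power, and one-sided tests would fit the directional wording. This tempers the exact figure. It does not restore 0.95: one-sided unadjusted power is 0.73, and the Sample size section claims no baseline correlation, let alone one near 0.78.

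Fourth, secondary hypotheses need not share the main power, and the Limitation section calls the study a pilot. Both are fair, and they are reasons not to enlarge the trial. They do not make the sizing statement accurate.

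**Conclusion.** The concern holds in this form: neither reading of 82 supports 0.95 power for the WS hypotheses. H2 and H3 each have about 0.61 power two-sided at d = 0.5 (0.73 one-sided), and 0.59 (0.71) after the planned attrition. The cause lies in the base statement. As a total, 82 gives 0.61. As a per-group number, it gives 0.89 two-sided or 0.94 one-sided for OUT v IN and leaves nothing for weather sensitivity.

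These figures assume alpha 0.05, an unadjusted comparison and an even WS split. A less even split lowers power, and baseline adjustment raises it by an amount the document does not let one calculate. The finding does not show that the trial is too small to run or that H2 and H3 cannot be studied. It shows that the stated justification does not describe what 164 patients deliver for them.

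**What to change.** Keep N = 164 and change the text.

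1. **Correct the base statement in Sample size.** Give alpha, sidedness, the test, any baseline correlation relied on, and whether 82 is per group or a total. Restate the power for OUT v IN: about 0.89 two-sided at 82 v 82 if no adjustment is claimed. This must be done together with item 2. Otherwise the section would give both 0.95 and about 0.6 for 82 patients at the same effect size.
2. **Remove the implication that doubling secures 0.95 for weather sensitivity.** State that H2 and H3 each rest on about 41 v 41 patients, with about 0.6 power at d = 0.5 two-sided and a detectable d of about 0.8 at power 0.95.
3. **Optionally, add an arm-by-WS interaction** on all patients in the planned General Linear Model, beside the two within-arm contrasts with confidence intervals. It suits hypotheses that predict opposite directions, but it does not replace H2 and H3: its power is about 0.89 only if both opposite effects of 0.5 hold, and about 0.36 if only one arm has an effect.

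The cost is wording in the Sample size section and, for item 3, in Statistical analysis. No patients, visits or measurements are added. The price is a less favourable stated power for H1, H2 and H3.
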